## Abstract

**Background:**

Preeclampsia and HELLP syndrome may have serious consequences for both mother and fetus. Women who have suffered from preeclampsia or the HELLP syndrome, have an increased risk of developing preeclampsia in a subsequent pregnancy. However, most women will develop no or only minor complications. In this study, we intend to determine cost-effectiveness of recurrence risk guided care versus care as usual in pregnant women with a history of early-onset preeclampsia.

**Methods/design:**

We developed a prediction model to estimate the individual risk of recurrence of early-onset preeclampsia and the HELLP syndrome. In a before-after study, pregnant women with preeclampsia or HELLP syndrome in their previous pregnancy receiving care as usual (before introduction of the prediction model) will be compared with women receiving recurrence risk guided care (after introduction of the prediction model).

Eligible and pregnant women will be recruited at six university hospitals and seven large non-university tertiary referral hospitals in the Netherlands.

The primary outcome measure is the recurrence of early-onset preeclampsia or HELLP syndrome in women allocated to the regular monitoring group.

For the economic evaluation, a modelling approach will be used. Costs and effects of recurrence risk guided care with those of care as usual will be compared by means of a decision model. Two incremental cost-effectiveness ratios will be calculated: 1) cost per Quality Adjusted Life Year (mother unit of analysis) and 2) cost per live born child (child unit of analysis).

**Discussion:**

This is, to our knowledge, the first study that evaluates prospectively the efficacy of a multivariable prediction rule for recurrent hypertensive disease in pregnancy. Results of this study could either be integrated into the current guideline on Hypertensive Disorders in Pregnancy, or be used to develop a new guideline.

## Background

### The disease

Preeclampsia is defined as de novo development of hypertension (> 140/90 mmHg) in combination with proteinuria after 20 weeks of gestation in pregnant women [1]. One of the most severe forms of this disease is called the HELLP syndrome, which is derived from the acronyms of the symptoms (Hemolysis, Elevated Liver enzymes and Low Platelets).

Preeclampsia (also termed early-onset preeclampsia) and HELLP syndrome may be life-threatening for both mother and child [2]. In the mother, these disorders predispose to premature cardiovascular disorders such as chronic hypertension, ischemic heart disease and stroke later in life [3]. Studies in children, born after preeclamptic pregnancies and who were relatively small at birth, have shown an increased risk of stroke in adult life, an increased risk of coronary heart disease and metabolic syndrome [4-6]. Preeclampsia and especially HELLP syndrome are perceived by patients and their partners as a highly traumatic life event, both during and after pregnancy [7].

In the United States and Europe, the prevalence of clinically relevant preeclampsia is approximately 2% of all pregnancies, with HELLP syndrome complicating preeclampsia approximately in 10 to 20% of the cases [3,8]. Maternal mortality rate in the Netherlands due to hypertensive disease during pregnancy amounts to 4.0 per 100,000 live births in 1993-2002 [9].

Although several risk factors have been identified, it is difficult to develop effective strategies for the prevention and treatment of these disorders [3]. Strategies applied nowadays are diverse and include antenatal surveillance, modification of lifestyle, dietary interventions and pharmacological therapy. In the last two decades, clinical guidelines for the management of preeclampsia and HELLP syndrome have been adopted in most developed countries [10-12].

Clinical management of preeclampsia or HELLP syndrome depends on the gestational age at onset, severity of symptoms, laboratory abnormalities, size and condition of the unborn infant, disease progression and response to symptomatic treatment.

Mild preeclampsia is usually managed expectantly, as opposed to the management of severe preeclampsia which is more pro-active consisting of the administration or magnesium sulphate, often combined with antihypertensives [13]. When gestational age is less than 34 weeks and both maternal and fetal condition are satisfactory, it is usually recommended to prolong pregnancy for at least 48 hours to benefit optimally from the enhancing effect of corticosteroid administration on fetal lung maturation. Fetal surveillance is an important component of the management. Delivery is the only causal treatment and therefore, the management of choice from 37 weeks' gestation onward [14,15].

### The health care problem

Although preeclampsia and HELLP syndrome are considered diseases of the first pregnancy, the risk of developing recurrent preeclampsia or HELLP syndrome is increased among parous women with preeclampsia and/or HELLP syndrome in their previous pregnancy. Sep et al. [16] conducted a literature search in order to identify prediction tests for recurrent disease. The recurrence rates reported vary from none to 31 percent for preeclampsia and from 3 percent to 7 percent for HELLP syndrome. Fortunately, the majority of women with a history of preeclampsia or HELLP syndrome have uncomplicated subsequent pregnancies.

To the best of our knowledge there is at this moment no consensus about the management of pregnant women with a history of early-onset preeclampsia or HELLP syndrome.

As a result, follow-up and counselling of these patients varies per centre, gynaecologist and patient, and is largely based on the perceived risk by the responsible care provider of recurrence of the disease in the next pregnancy and the level of anxiety of the patient and its resulting demand for care. Formerly preeclamptic patients are often subjected to various medical screening programmes to detect associated disorders, followed by additional exams by other specialists or the initiation of some management (postpartum evaluation). During a next pregnancy, care varies from regular surveillance by the gynaecologist to intensive surveillance and counselling in order to identify the onset of adverse pregnancy course as early as possible.

### Motivation and relevance for the study

This lack of uniformity in the treatment of these patients asks for more standardisation, e.g. by providing care tailored to the individualised risk assessment.

Current policy may not be efficient. Since only a small percentage of these women develop early-onset recurrent disease in their next pregnancy, clinical management in the next pregnancy may benefit from subdividing these women into subgroups with or without increased risk. The care provided to these women can then be adjusted to their actual risk profile. Particularly former patients at low risk are expected to benefit from this type of risk stratification. Recurrence risk guided care could lead to a substantial reduction of (health care) costs and an increased quality of care.

We have recently developed a multiple-factor model for the prediction of recurrent early-onset preeclampsia and/or HELLP syndrome during the current pregnancy in women with a prior pregnancy complicated by preeclampsia and/or HELLP syndrome ([name], [name], [name], [name], [name], [name], [name], [name], [name], [name], [name], [name], [name], [name]: A preconceptional prediction model for recurrent early-onset preeclampsia and the HELLP syndrome, unpublished).

The PreCare study (pregnant women with previous preeclampsia: efficiency of care based on recurrence risk estimation), was designed to (1) estimate cost-effectiveness of recurrence risk guided care versus care as usual for pregnant women with a previous pregnancy being complicated by preeclampsia or HELLP syndrome and (2) to validate the prediction model externally on the basis of the results of a prospective cohort and to update the prediction model if necessary. To this end, we will use the prediction model to differentiate the intensity of monitoring of pregnant women with a history of early-onset preeclampsia and/or HELLP syndrome. Patients are assigned to either the 'regular monitoring' or 'intensive monitoring' protocol. We will compare this strategy, referred to as recurrence risk guided care, with usual care for these patients in The Netherlands.

For this purpose, the following research questions were specified:

1. What are the effects of recurrence risk guided care versus care as usual for pregnant women with a previous preeclamptic pregnancy, on maternal and fetal morbidity and mortality?

2. What are the effects of recurrence risk guided care versus care as usual on specific and generic quality of life, anxiety, depression and development of posttraumatic stress?

3. What are the societal costs associated with the effects of recurrence risk guided care versus care as usual?

4. What is the cost-effectiveness of recurrence risk guided care versus care as usual?

### Development of prediction model

Although earlier studies have identified individual predictive factors for recurrent preeclampsia, a combination of variables for the prediction of recurrent preeclampsia has not been explored until recently. A simple prepregnant prediction rule which includes several predictive factors was developed by Sep et al. [17]. Unfortunately, patient data were collected from a single hospital and the number of included patients was limited (n = 186).

We developed a prediction model to estimate the individual recurrence risk of recurrence of early-onset preeclampsia and/or the HELLP syndrome. We used data of 407 women with early-onset preeclampsia and/or the HELLP syndrome in their first pregnancy, who had undergone subsequent postpartum screening and who had a recorded consecutive ongoing pregnancy for which maternal and neonatal outcomes were available. Data were collected from four university hospitals (Maastricht University Medical Centre, University Medical Centre Utrecht, Academic Medical Centre Amsterdam and University Medical Centre St. Radboud Nijmegen), and one tertiary referral hospital (Máxima Medical Centre Veldhoven).

Predictors of recurrent disease were preselected based on availability in the five different hospitals, previous literature and gynaecologists' expert opinion. Fasting circulating level of glucose measured at postpartum screening, gestational age at delivery of the first pregnancy, prior small-for-gestational-age newborn, chronic hypertension and maternal BMI before the second pregnancy proved to be the predictors within a logistic regression model ([name], [name], [name], [name], [name], [name], [name], [name], [name], [name], [name], [name], [name], [name]: A preconceptional prediction model for recurrent early-onset preeclampsia and the HELLP syndrome, unpublished).

Since a model tends to perform best in the derivation sample, called 'overfitting', we used bootstrapping techniques to internally validate the model. A shrinkage factor was computed to shrink the regression coefficients in order to get a more conservative risk estimate.

## Methods/design

### Design

The PreCare study uses a before-after design, in which outcomes and costs before the introduction of the prediction model (i.e. care as usual) are compared with outcomes and costs after introduction of the prediction model (i.e. recurrence risk guided care).

This study consists of two consecutive phases. In the first phase of the study, 50 women receiving care as usual will be followed prospectively from their first pregnancy-related outpatient visit until 3 months post partum. These 50 women will receive questionnaires in order to measure quality of life, anxiety, depression, posttraumatic stress and costs outside the hospital. Retrospective data of an additional group of 200 women who have been treated with care as usual in the past will be collected later on. Then the prediction rule will be introduced. In the second phase, 250 women will receive either protocolised regular monitoring or protocolised intensive monitoring depending on their risk of developing early-onset preeclampsia or HELLP syndrome during their current pregnancy, as estimated on the basis of the prediction model. In regular monitoring, pregnant women are monitored less intensively than in intensive monitoring. Regular monitoring and intensive monitoring are described in detail in the 'Monitoring protocols' section. Figure 1 summarises the design.

**Figure 1 F1:**
[figure not shown]
**Design of the study**.

### Participants/eligibility criteria

In phase 1 and 2, pregnant women (aged 18 years and older) with preeclampsia and/or HELLP syndrome in their previous pregnancy who have visited the outpatient clinic until 16+6 weeks of pregnancy are eligible for participation in the PreCare study.

Given these general eligibility criteria, two subgroups are distinguished in recurrence risk guided care (phase 2).

In women who gave birth after early-onset preeclampsia or HELLP syndrome until 33+6 weeks gestational age in the previous pregnancy, the prediction model is applied in order to allocate the participants to one of the two monitoring protocols. The data which are required as input parameters for the prediction model should be available. These variables mostly come from the postpartum evaluation.

Women who gave birth between 34 and 36+6 weeks gestational age in the previous pregnancy face a relatively small risk of developing recurrent preeclampsia or HELLP syndrome, compared to women who gave birth before 34 weeks. Therefore, they all are allocated to the regular monitoring subgroup [18].

Women suffering from severe co-morbidity, such as diabetes mellitus, SLE, renal disease, cardiac disease or anti-phospholipids syndrome are excluded from the study as they will all receive (or have received where it concerns the retrospective patients) intensive surveillance. The current study will not include women who gave birth after 37 weeks gestational age.

The study population is recruited from six university hospitals and seven large non-university tertiary referral hospitals in the Netherlands: the Maastricht University Medical Centre, University Medical Centre St. Radboud Nijmegen, the Isala Clinics Zwolle, Erasmus Medical Centre Rotterdam, Academic Medical Centre Amsterdam, University Medical Centre Utrecht, Máxima Medical Centre Veldhoven, the University Medical Centre Groningen, Martini Hospital Groningen, Amphia Hospital Breda, Atrium Medical Centre Heerlen, Jeroen Bosch Hospital Den Bosch and Kennemer Hospital Haarlem.

### Recruitment procedures

For the prospective assessment, 50 care as usual patients and 250 recurrence risk guided patients will be included in the study.

The research nurse or the gynaecologist of participating hospitals identifies eligible women by screening the appointment system of the outpatient clinic. After the pregnant woman has given informed consent for participation in the study, patients in phase 1 will be enrolled in care as usual whereas patients in phase 2 will be enrolled in recurrence risk guided care.

In recurrence risk guided care (phase 2), a simple web based risk calculator for the determination of recurrence risk and required intensity of surveillance has been developed and has been made accessible to gynaecologists and research nurses.

Information about the recommended components of intensive monitoring and regular monitoring has been provided together with the risk calculator.

For the retrospective assessment, 200 patients who were treated according to care as usual will be used as a comparator group based on matching. Matching criteria will at least include maternal age (difference < 5 years) and gestational age at delivery. Consequently, at study completion, there will be 250 care as usual patients who will be compared with 250 recurrence risk guided patients.

### Data collection

For the prospective assessment (n = 50 care as usual; n = 250 recurrence risk guided care), baseline demographics, past obstetric and medical history will be recorded in case report forms. Information is obtained on the condition of mother and child, infant weight, infant length, morbidity and mortality from the infant and maternal records. If applicable, details of the admittance of the child to the neonatal intensive care, high care or medium care unit will also be collected. All activities in the hospital will be documented until three months postpartum.

We will assess not only clinical outcomes, but also health-related quality of life by using the EQ-5 D [19], anxiety by using the STAI [20], depression by using the Beck Depression Inventory [21] and posttraumatic stress by using the PTSD Symptom Scale [22]. The QoL questionnaires will be administered at 3-month intervals between baseline (before 20 weeks of pregnancy), at 29 weeks of pregnancy, ten days and three months postpartum. Costs outside the hospital, such as GP care, midwife and maternity care, productivity losses and out-of-pocket expenses will be obtained by means of a retrospective cost questionnaire with a recall period of 3 months. Long-term follow up of the women and children may be possible, but is not included in the current study.

For women enrolled in the retrospective assessment (n = 200), all data described above will be collected, except data on health-related quality of life, anxiety, depression, posttraumatic stress and costs outside the hospital.

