#### Intensive monitoring

Women will visit the outpatient clinic 14 - 16 times: (8, 12), 16, 18, 20, 22, 24, 26, 28, 30, 32, 34, 36, 38, 39 and 40 weeks gestational age.

At two occasions during an intensive monitoring pregnancy (16 and 20 weeks), the patient will undergo a series of diagnostic tests, which consist of

1. Measurements in urine: (micro)albuminuria, creatinine, protein (protein serves to calculate the protein-to-creatinine ratio)

2. Measurements in blood: Haemoglobin, platelet count, mean platelet volume, creatinine, urate, CRP, glucose, fibronectin, Flt-1, endoglin

3. 24 h blood pressure monitoring. This assessment is optional (not obligatory)

4. Assessment of the Doppler flow velocity profile in both uterine arteries (at 20 weeks)

Activities other than, or additional to those described in the regular monitoring and intensive monitoring protocols (such as intercurrent admissions, additional outpatient visits or diagnostic testing, or telephone/e-mail contacts) will be registered.

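### The baseline questionnaire window runs past the point of risk allocation, so a guided woman's baseline scores can be taken after her monitoring group is known and differentiated care has begun

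*Protocol article*

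**What the plan says.** All references are to the protocol article.

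- **Data collection.** EQ-5D, STAI, Beck Depression Inventory and PTSD Symptom Scale are first given at "baseline (before 20 weeks of pregnancy", then at 29 weeks, ten days postpartum and three months postpartum. The baseline has only an upper limit. The 50 prospective usual-care women and the 250 guided women complete these questionnaires; the 200 retrospective women do not.
- **Participants/eligibility criteria.** Women "who have visited the outpatient clinic until 16+6 weeks of pregnancy are eligible for participation". For those whose previous delivery was at or before 33+6 weeks, "the prediction model is applied in order to allocate the participants to one of the two monitoring protocols". For those who delivered at 34 to 36+6 weeks, the text says: "Therefore, they all are allocated to the regular monitoring subgroup".
- **Recruitment procedures.** After consent, phase 1 women enter care as usual, "whereas patients in phase 2 will be enrolled in recurrence risk guided care". The questionnaire is not placed in this sequence.
- **Regular monitoring and Intensive monitoring.** Before 20 weeks, regular monitoring has visits at (8, 12) and 16 weeks; intensive monitoring has (8, 12), 16 and 18. Diagnostic tests are added in the intensive protocol only: "At two occasions during an intensive monitoring pregnancy (16 and 20 weeks".
- **Motivation and relevance for the study.** Research question 2 asks for the effect of guided care on "specific and generic quality of life, anxiety, depression and development of posttraumatic stress".

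**The concern.** A baseline score should be taken before the intervention can act on it. Here the intervention is the risk-based assignment and the monitoring that follows, and both can begin while the baseline window is still open. Learning that one is in the regular or the intensive group could plausibly move anxiety or quality of life at once. The Background section itself connects perceived risk, patient anxiety and demand for care.

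The design makes this more important than it would be in a randomised trial. The comparison is before-after, and only 50 usual-care women supply these scores. Their baseline is the only direct evidence that the two cohorts were psychologically alike before guided care began. A baseline that already carries part of the effect weakens that check. It also removes part of the effect if it is used for change scores or as a covariate. EQ-5D additionally feeds the cost per QALY for the mother, one of the two main cost-effectiveness ratios.

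**Working it through.** The plan states no figure to reproduce. The check is one of timing, followed by an illustration on stated assumptions.

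**1. Must allocation precede 20 weeks?** The two visit schedules coincide through the 16-week visit. They differ from the 16-week test series onward, and again at the 18-week visit. Neither intensive-only component can be delivered as scheduled unless the woman has been assigned by then. This does not depend on treating 16+6 weeks as an allocation date.

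**2. How late can a baseline fall?** The last permitted day is 19+6, that is 19 × 7 + 6 = 139 days.

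| Allocation at | Day | Days to 19+6 |
|---|---|---|
| 16+6 | 118 | 139 − 118 = 21 |
| 16+0 | 112 | 139 − 112 = 27 |
| 8+0 | 56 | 139 − 56 = 83 |

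The 83 days apply only if a woman is allocated at an 8-week visit, and they measure time since allocation. Exposure to care that differs between the two protocols starts at 16 weeks, so before the window closes it is at most 27 days. In that time a woman on intensive monitoring can have had the first test series and the 16- and 18-week visits. A woman on regular monitoring can have had her 16-week visit knowing her group.

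**3. Does the interval wording help?** The questionnaires are described as three months apart. Counting back about 13 weeks from 29 weeks gives 29 − 13 = 16 weeks. That is about when differentiated care starts, so it does not secure a baseline before allocation.

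**4. What could be lost (assumptions, not in the document)?** Let D be the effect at follow-up, f the share of guided women with a post-allocation baseline, and s the share of D already present in those baselines. Assume usual-care baselines are unaffected.

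- Change-score contrast: D − f·s·D, so the fraction retained is 1 − f·s.
- Baseline-adjusted contrast, with baseline–follow-up correlation ρ and equal standard deviations: the fraction retained is about 1 − ρ·f·s.

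| f = s | Change score retains | Adjusted retains (ρ = 0.6 assumed) |
|---|---|---|
| 0.25 | 1 − 0.0625 = 94% | 1 − 0.0375 = 96% |
| 0.5 | 1 − 0.25 = 75% | 1 − 0.15 = 85% |
| 1 | 0% | 40% |

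The range runs from negligible to severe, and nothing in the document locates the study within it.

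**The case against.** The strongest reply is that the order of consent, questionnaire, calculation and disclosure is operational detail that an article leaves to the full protocol, and that the figure on the process of guided care, not reproduced in the text available here, may show it. An upper limit of 20 weeks instructs nobody to collect baselines late. This stands in part: the text permits a post-allocation baseline but does not say that one will occur. Still, the window is stated, it overlaps the scheduled intensive care, and no visible passage closes the overlap.

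Several stronger readings are tempting and are not supported:

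- *Allocation is complete by 16+6 weeks.* That limit applies to the qualifying clinic visit. No allocation date is given.
- *Every guided woman receives a new risk result before baseline.* Women who delivered at 34 to 36+6 weeks are assigned by history, without the model. The document does not say when, or in what form, women are told.
- *The usual-care baseline is clean and only the guided arm is affected.* The Background section says usual follow-up and counselling already depend largely on the risk perceived by the care provider. Phase 1 women may also be counselled before 20 weeks, though without a model-based assignment.
- *A third or a half of the effect is lost.* That needs assumed values for f and ρ, and an effect that is wholly immediate and persistent. The Data analysis section does not say that baseline scores enter as a covariate or a change-score reference. Regular and intensive assignment could also move anxiety in opposite directions and partly cancel, so even the direction of bias is open.

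**Conclusion.** The concern holds as a weakness in a stated measurement window. A baseline is allowed up to 21 days after an allocation at 16+6 weeks, 27 days after one at 16+0, and longer if the woman is allocated earlier. This rests on the stated windows and on the intensive protocol being delivered as scheduled. Whether it biases results depends on how often it happens and how the scores are used, and the document gives neither, so no size or direction can be assigned. It affects the research question 2 outcomes and maternal QALYs, in a comparison of 250 guided with 50 usual-care women. The primary outcome, recurrence of early-onset preeclampsia or HELLP syndrome, is not touched. It is worth correcting before phase 2 enrolment because a score from before allocation cannot be recovered afterwards.

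**What to change.** - In both phases, have the baseline questionnaire completed at consent. In phase 2, complete it before the risk result or monitoring group is disclosed, including for women assigned by history. The possible overlap then falls to zero days.
- Record the questionnaire completion date in both phases and, in phase 2, the allocation and disclosure dates.
- Handle any baseline completed after allocation in a sensitivity analysis. Do not simply drop such baselines from adjustment: phase 1 has no disclosure date, so that rule would create missing covariates in the guided arm only.

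The cost is a change in the order of steps at enrolment and the recording of these dates. The downside is a small delay in telling the woman her monitoring group. The monitoring protocols themselves are unchanged.
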